## Abstract

**Background:**

Up to 42% of all stroke patients do not get out of the house as much as they would like. This can impede a person’s quality of life. This study is testing the clinical effectiveness and cost effectiveness of a new outdoor mobility rehabilitation intervention by comparing it to usual care.

**Methods/design:**

This is a multi-centre parallel group individually randomised, controlled trial. At least 506 participants will be recruited through 15 primary and secondary care settings and will be eligible if they are over 18 years of age, have had a stroke and wish to get out of the house more often. Participants are being randomly allocated to either the intervention group or the control group. Intervention group participants receive up to 12 rehabilitation outdoor mobility sessions over up to four months. The main component of the intervention is repeated practice of outdoor mobility with a therapist. Control group participants are receiving the usual intervention for outdoor mobility limitations: verbal advice and provision of leaflets provided over one session.

Outcome measures are being collected using postal questionnaires, travel calendars and by independent assessors. The primary outcome measure is the Social Function domain of the SF36v2 quality of life assessment six months after recruitment. The secondary outcome measures include: functional ability, mobility, the number of journeys (monthly travel diaries), satisfaction with outdoor mobility, mood, health-related quality of life, resource use of health and social care. Carer mood information is also being collected.

The mean Social Function score of the SF-36v2 will be compared between treatment arms using a multiple membership form of mixed effects multiple regression analysis adjusting for centre (as a fixed effect), age and baseline Social Function score as covariates and therapist as a multiple membership random effect. Regression coefficients and 95% confidence intervals will be presented.

**Discussion:**

This study protocol describes a pragmatic randomised controlled trial that will hopefully provide robust evidence of the benefit of outdoor mobility interventions after stroke for clinicians working in the community. The results will be available towards the end of 2012.

**Trial registration:**

ISRCTN58683841

## Background

Stroke can have a devastating effect on people's lives, with half of survivors being dependent on others six months later [1], one third feeling socially isolated, one quarter having abnormal mood and half not getting out of their house as much as they would like. These are worldwide health care issues which affect many people. A total of 130,000 people a year have a stroke in England and Wales (Office of National Statistics 2001). Community based research over the last three decades has shown that people living at home with stroke have felt neglected, not provided with the correct information and have received patchy levels of rehabilitation [2]. The NHS has developed guidelines through the National Service Framework for Older People [3] and the National Clinical Stroke Guidelines [4] to help commissioners and therapists provide evidence-based practice. However, within these documents there is very little information about the long-term rehabilitation that should be provided because the research evidence is not available to help make robust recommendations.

A single centre randomised controlled trial which evaluated an outdoor mobility rehabilitation intervention found clear outdoor mobility benefits for those people who received the intervention [5]. The generalisability of the study was limited as the intervention was delivered by a single therapist, in one city and there was no economic evaluation. Our single centre trial provided confirmation that we were asking a relevant and important question and that the intervention could be implemented within existing NHS structures. This present multi-centre trial was planned to evaluate the clinical and economic effectiveness of the intervention before we can recommend its wider adoption.

## Methods/design

### Trial purpose

The trial’s purpose was to confirm or refute the clinical effectiveness and cost effectiveness of treating stroke patients with outdoor mobility limitations with a novel targeted rehabilitation therapy intervention versus standard clinical practice.

### Trial objectives

The health care objective is to improve the quality of people’s lives after a stroke by enabling them to get out of the house more often and when they wish.

The research objective is to test the effectiveness and cost effectiveness of treating people who have had a stroke with a new outdoor mobility rehabilitation intervention.

### Trial design

This is a multi-centre parallel group randomised, controlled trial. The trial consists of an initial baseline visit to provide information and explain the study, take informed consent, provide the routine clinical stroke rehabilitation treatment, complete a set of questionnaires and provide a travel diary with instructions. Randomization to the control or intervention group is stratified by age (<65 years and ≥65 years) and site. The intervention group are receiving up to 12 intervention visits within four months from recruitment. All participants are completing monthly travel diaries and questionnaires at 6 and 12 months.

### Site and participant recruitment

We planned to have 15 NHS community or Primary or Secondary Care Trust study sites throughout England, Scotland and Wales. People who have had a stroke were identified between November 2009 and July 2011 through GP practices, primary care therapy teams and community stroke teams. A letter along with study information was sent to the identified stroke patients by a member of their normal clinical care team, asking if they were interested in taking part in the study. The letter contained a reply slip and a reply paid envelope. If the potential participant was interested in taking part, they completed the slip and returned it in the envelope directly to the local stroke/therapy team, who then informed the local Research Assistant (RA). The RA then contacted the patient to arrange an appointment to discuss the study further and respond to any questions. If needed, an interpreter, translator or signing service was available. The RA explained the details of the trial and provided a Participant Information Sheet, ensuring that the participant had sufficient time to consider whether or not to participate.

### Informed consent

It was explained to the potential participant that their entry into the trial was entirely voluntary and that their treatment and care would not be affected by their decision. It was also explained that they could withdraw at any time. In the event of their withdrawal, it was explained that their data collected so far could not be erased and would be used in the final analyses. If they agreed to participate in the study, the RA asked the participant to give written consent before they underwent any interventions related to the study that would not have formed part of their normal care. Those participants unable to sign the consent form were asked to mark the form and a witness (either Carer or other person present) also signed the relevant section on the consent form. One copy was kept by the participant, one by the Investigator, and a third retained in the patient’s GP records. With the consent of the participant the research team informed the participant's GP about their participation in the clinical trial.

### Inclusion criteria

Patients were eligible for the study if they provide written informed consent and if they: (i) are aged 18 years or over; (ii) have had a stroke at least 6 weeks previously and (iii) wish to get out of the house more often.

### Exclusion criteria

Patients were not eligible for the study if they: (i) were not able to comply with the requirements of the protocol and therapy program, in the opinion of the assessor; (ii) still in post-stroke intermediate care or active rehabilitation or (iii) were previously enrolled in this study.

### Outcome measures

#### Baseline

The RA collected basic demographics required for randomisation from each participant at the baseline visit. The baseline assessment questionnaires were completed while the RA was present and returned to the trial coordinating centre. The basic demographics, including the NHS number were recorded and supplied to the NHS IC/NHS Central Register to allow mortality checks prior to follow-up.

#### Assessment questionnaires

The 6- and 12-month assessment questionnaires are being posted to the participants along with reply paid envelopes. If the assessments have not been returned within 2 to 3 weeks of the 6- or 12-month timeline then the participant is contacted by telephone by a member of the research team to remind them. Finally, if two to three weeks later the assessments have still not been returned, then the blinded-to-intervention RA arranges to visit the participant and assist in completing the questionnaires. Using this method, a 90% return rate of active participants (that is, those which had not withdrawn, died or been lost to follow-up) was found in the previous single centre trial with the further 10% collected by an independent assessor.

#### Travel diaries

A travel diary is being completed by all participants on a monthly basis. This is in the form of a calendar with the participants entering the number of journeys made on the calendar for that particular day. In addition, in order for the study team to assess safety, participants indicate when they have had a fall on a particular day. The participant is provided with 12 calendar months’ worth of travel diary. Training is provided at baseline assessment in the completion and return of the travel diaries. At the end of each month participants are asked to return that month of the calendar to the research team. A reminder letter is sent to the participant, along with a reply paid envelope, a short time before the previous month’s diary is due for return.

#### Primary outcome measure

The social function domain score of the SF-36v2 [6] measured at six months. This is one of the eight domains of the SF-36v2 and is scored and transformed on to a scale 0 (worst possible health state) to 100 (best possible health state).

The secondary outcome measures at 6 and 12 months are: (i) Nottingham Extended Activities of Daily Living Scale [7] (a measure of functional ability). (ii) Rivermead Mobility Index (a measure of mobility) [8]. (iii) Travel Diary (number of journeys). (iv) Yes or no question: "Do you get out of the house as much as you would like?" (Satisfaction with outdoor mobility). (v) General Health Questionnaire 12 (GHQ-12) [9] (measure of participant mood). (vi) GHQ-12 [9] (measure of Carer mood).(vii) EQ-5D [10] and SF-6D (subset of SF-36 v2 [6]) (viii) Resource use of health and social care and provision of equipment. (ix) Participant mortality (death data) will be collected from NHS IC/NHS Central Register.

#### Carer assessment

Part of the study is to assess if any benefits to the participants are allied with benefits to their carer. For this study, the definition of a carer is “someone who provides unpaid care by looking after a family member, friend or partner following stroke”. In order to assess this, we are asking the carer, if applicable, to complete the GHQ-12 questionnaire at baseline, 6 months and 12 months. The RA first asks the participant if they would like their carer to be asked about completing this questionnaire. We provide a carer information sheet, though we do not ask them to provide informed consent as completion of the questionnaire will be seen as implied consent. This is explained to the carer.

### Health economics

The consequences in terms of patient-specific resource use will be measured using responses to the 6- and 12-month assessments; this will capture information on quantity of primary and secondary health care use, use of personal social services and some patient/carer costs.

Unit costs will be derived from routine published cost data sources, such as the PSSRU health and social care costs [11] and NHS Reference Costs [12] using a common price year. This will enable the overall management cost of treatment to be calculated for each patient and, in turn, the incremental mean cost associated with the intervention compared to control to be estimated. A cost utility analysis will be undertaken measuring health-related quality of life using both the EuroQol EQ-5D [10] and SF-6D [6].

### Randomisation

Randomisation is based on a computer generated pseudo-random code using random permuted balanced blocks of randomly varying size, created by the Nottingham Clinical Trials Unit (NCTU) in accordance with their standard operating procedure (SOP) and held on a secure server. The randomisation is stratified by age (<65 years and ≥65 years) and site. Sixty-five years of age was chosen because Mobility Allowance, a monetary allowance is only available under this age and is often used to purchase a car. This is not available for people over 65 years of age. All participants are given the control group standard information prior to randomization in order to minimize performance bias and reduce contamination. Participants are randomly allocated (1:1 ratio) to either the intervention or to the control group. Access to the sequence is confined to the NCTU Data Manager (who is independent from the study team). Investigators/sites access the treatment allocation for each participant by means of a remote, secure, internet-based randomisation system developed and maintained by the NCTU. The sequence of treatment allocations is concealed until interventions have all been assigned and recruitment, data collection and all other trial-related assessments are complete. After confirming study eligibility and obtaining informed consent, the investigator enters basic demographic details into the web-based randomization program. Once these details have been entered irrevocably into the program, the group to which the patient is randomly allocated is provided to the investigator.

### Minimization of bias and maximising blinding

We have taken every step to maintain blinding for the outcome assessments by using postal questionnaires and RAs. Following any visits, at 6 and 12 months, to assist with questionnaire completion, the RA completes a blinding questionnaire to assess if the blinding has been broken. The data are entered, stored and managed by the NCTU until the end of the trial. We are recruiting participants from numerous sites across the UK to reduce response bias and we are using numerous rehabilitation staff to reduce expertise bias.

### Maintenance of randomisation codes and procedures for breaking code

Neither the participants nor the therapist are blinded to which treatment the participants receive. The RA is blind, though there is no foreseeable situation whereby they would need to know the treatment allocation of a particular participant. The outcome assessors are blind, but again there is no requirement for them to know the treatment allocation at any stage. As a result there is no procedure in place for breaking the randomisation code. The statistician analysing the data is also blind and allocations will not be revealed until all data analyses have been completed.

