#### Intervention group

Participants receive what is considered clinically to be routine intervention for outdoor mobility limitations. That is, verbal advice and provision of leaflets provided during the baseline assessment visit. In addition, participants in this group receive up to 12 rehabilitation outdoor mobility sessions of about an hour each over four months. Development of this intervention followed the guidelines for complex interventions [13] using qualitative research findings [14] in the pre-clinical stage to develop ‘barriers and need’ theories. The intervention aims to increase outdoor mobility participation by alleviating physical difficulties, develop skills to maximize the individual's potential and to overcome psychological barriers. A description of the intervention has been published [15]. The main component of the intervention is that therapists go repeatedly with patients to try outdoor mobility, including buses, taxis, walking, voluntary drivers and mobility scooters until they feel confident to go alone or with a companion. The number of interventions depends entirely on the participant. If they feel they do not require any further interventions, for whatever reason, then the interventions can stop. If they feel they require additional intervention, for whatever reason, they can continue the intervention, up to a maximum of 12 visits.

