#### Control group

Participants receive what is considered clinically to be routine intervention for outdoor mobility limitations. That is, verbal advice and provision of leaflets provided during the baseline assessment visit.

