### Assessment of efficacy

#### Analysing primary outcomes

The mean Social Function score of the SF-36v2 will be compared between treatment arms using a multiple membership form of mixed effects, multiple regression analysis adjusting for centre (as a fixed effect), age and baseline Social Function score as covariates and therapist as a multiple membership random effect. Regression coefficients and 95% confidence intervals will be presented. The robustness of these findings will be assessed by repeating the analysis and including baseline variables (such as gender) that are associated with the outcome variable as covariates in the model.

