#### Analysing secondary outcomes

The outcome variables mobility measured with the Rivermead Mobility Index [8] number of outdoor journeys taken, functional ability measured by the Nottingham Extended Activities of Daily Living Scale [19]; mood and carer psychological distress measured by the General Health Questionnaire 12 [9] will be analysed using the same method as for the primary outcome measure. In all analyses, an adjustment for centre, therapist effect, age and baseline value will be made.

The proportion of participants saying they get out of the house as often as they would like will be compared between treatment arms using a mixed effects logistic regression analysis adjusting for centre (as a fixed effect), age and whether or not they get out of the house as often as they would like as recorded at baseline. Odds ratios and 95% confidence intervals will be presented.

The robustness of the findings for all secondary outcomes will be assessed by repeating the analysis and including baseline variables, (such as gender), that are associated with the outcome variable as covariates in the model.

We acknowledge the potential for type 1 errors associated with significance testing for multiple end points. We will, therefore, consider our analyses of the secondary outcome measures to be partly exploratory in nature, and partly confirmatory of our findings for the primary outcome measure.

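### The analysing statistician's blind cannot last through all analyses as stated, because the main models need therapist links that are described after randomisation only in the intervention arm

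*Protocol article*

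**What the plan says.** On blinding, the protocol article (Maintenance of randomisation codes and procedures for breaking code) says of the analyst: "The statistician analysing the data is also blind and allocations will not be revealed until all data analyses have been completed". No stage or type of analysis is excepted.

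On the primary model, the section Analysing primary outcomes adjusts for centre as a fixed effect, with "age and baseline Social Function score as covariates and therapist as a multiple membership random effect". The same section plans a robustness repeat "including baseline variables (such as gender) that are associated with the outcome variable as covariates in the model". The section Analysing secondary outcomes carries the method over to mobility, journeys, functional ability, participant mood and carer mood, and adds: "In all analyses, an adjustment for centre, therapist effect, age and baseline value will be made".

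On who sees a therapist, the Intervention group section says: "In addition, participants in this group receive up to 12 rehabilitation outdoor mobility sessions of about an hour each over four months". It also says: "The main component of the intervention is that therapists go repeatedly with patients to try outdoor mobility". For controls the article describes routine care only: "That is, verbal advice and provision of leaflets provided during the baseline assessment visit". Under Randomisation, both arms receive that standard information before they are allocated.

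**The concern.** A multiple-membership model cannot be fitted from an arm code and an outcome alone. It needs, for each participant, the therapists who treated them and the share of contact that each provided. If such links arise after randomisation in one arm only, the variable that the model requires also identifies that arm. Labelling the arms A and B does not help, because only one label will carry therapist links.

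Two things are at stake. First, the trial report would claim a blind that did not hold when the primary analysis was run. Participants and therapists are unblinded and the primary outcome is self-reported, so readers may give weight to the analyst's blind. Second, some modelling choices are made with outcome data in hand, and the article as written would let someone who can see the arms make them.

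**Working it through.** The article gives no figure for this point, so the check is to trace the data that the planned models need and the arm in which those data can arise.

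**Step 1: data needed to fit the models.**
- Therapist identifiers and membership weights per participant (Analysing primary outcomes; Analysing secondary outcomes).
- An arm label, at least coded. The primary model compares arms, and the section on missing, unused and spurious data imputes separately by group.

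**Step 2: where those data arise.**

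| Source of therapist contact | Intervention | Control |
|---|---|---|
| Advice and leaflets at the baseline visit, before allocation | yes | yes |
| Sessions after randomisation (at most 12) | yes | none described |
| Treatment records kept by the staff who deliver it (Fidelity of treatment) | yes | none described |

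A further field points the same way if it is in the analysis file. Under Assessment of safety and adverse events, the only adverse events recorded are falls in the intervention group that needed help from a healthcare professional.

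**Step 3: how many participants are identified.** Planned size is 506, or 253 per arm (Sample size and justification).

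- *Therapist links beside a coded arm label.* One code has links and the other has none, so the code is read off for everyone: 253 + 253 = 506. This includes intervention participants who had no session, because they share the code of those who did.
- *Therapist links alone.* Let s be the share of the intervention arm with at least one session. The article gives no value, so the values of s below are assumptions. Treated participants identified = 253 × s. Share of those without links who are controls = 253 / (253 + 253 × (1 − s)).
  - s = 1.0: 253 identified; 253/253 = 100%
  - s = 0.9: 227.7, about 228 identified; 253/278.3 = 91%
  - s = 0.8: 202.4, about 202 identified; 253/303.6 = 83%

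The first case is the relevant one for the primary fit, which needs both fields.

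**Step 4: what an unblinded analyst could still influence.**
- Primary model: centre, age, baseline score and therapist are named in advance, so there is little room.
- Robustness models: extra baseline covariates are picked by their association with the outcome, for the primary and all secondary outcomes. This choice is open in the article.
- Multiple imputation: a sensitivity analysis after complete-case analysis, with the imputation model not stated in the article.

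**The case against.** The strongest objections concern certainty and consequence.

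*The premise is inferred.* The article never says that therapist identifiers exist only in the intervention arm, and it does not name who gives the baseline advice. The abstract calls control care one session, so a provider code for controls is possible. This stands as a limit on certainty, and it is why the conclusion says in all likelihood. It does not rescue the statement. The baseline advice goes to both arms before allocation, the article places the research assistant at that visit, and later sessions and their weights would still generally separate the arms.

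*Other safeguards exist.* A reader might infer that the blind is all that protects the open choices, or that the primary estimate is at risk. The documents support neither reading. The Statistical analysis section says that a full analysis plan was produced and agreed with the Trial Steering Group, and that the 6-month data wait until all data are collected. The primary model's terms are fixed. The normal-versus-skewed judgement, as the article states it, decides only which descriptive summaries are shown.

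*All 506 unmasked is too strong.* Without an arm label, intervention participants who had no session look like controls. That is correct, and the figure of 506 applies only when a coded label sits beside the links.

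*Masking is a matter for the analysis plan.* Its mechanics are, and their absence from an article is no fault. The point here is a positive statement that the article's own model defeats. Scrambled codes during programming could protect earlier stages, but the final fit needs the real links, so they cannot carry the blind through all analyses. A separate person running the therapist models might, but the article describes no such arrangement.

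**Conclusion.** The blinding statement is wrong as written. Taken with the therapist effect in the primary and continuous secondary models, the blind cannot last until every analysis is complete. Fitting those models in all likelihood reveals treated participants, and with a coded arm label it reveals both arms (506 planned). This rests on one inference: that controls have no therapist links after randomisation. The article supports it but does not state it.

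The practical exposure is limited, mainly to the outcome-associated covariates in the robustness models and to the imputation model for the sensitivity analysis. The unseen analysis plan may narrow even these. No estimate, sample size or primary-model term changes, and the size of any resulting bias cannot be computed from the document. The correction is worth making because the report would otherwise repeat a blinding claim that does not hold.

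**What to change.** Restate the sentence in the section on maintenance of randomisation codes along these lines: the statistician works blind, on a dataset without therapist links, session counts or the intervention-only adverse-event field, until the database is locked and until the additional baseline covariates and the imputation model are fixed. The independent data manager then releases the therapist file. The report states that the statistician was potentially unblinded from that point.

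This is workable. Association between baseline variables and the outcome can be judged without arm or therapist data, analysis already waits for complete data collection, and the data manager who holds the allocation sequence is independent of the study team. The cost is a change of wording and a two-step data release. The small downside is that the report can no longer claim blinding through all analyses.
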